### 11.1.2.2. Baseline characteristics

The number of women screened and enrolled or excluded will be summarized by reason for exclusion. For the women enrolled in the study, the number of women discontinued or lost-to follow-up will be tabulated by reason and visit of study discontinuation. This information will be summarized in a CONSORT flow diagram.

Patients in each treatment group will be described with respect to baseline characteristics. The description will be in terms of medians and interquartile ranges for continuous characteristics and using counts and percentages for categorical characteristics. The clinical importance of any imbalance will be noted but statistical tests of significance of baseline imbalance will not be undertaken.

### 11.1.2.3. Primary analysis

The primary analysis is based on the qPCR vaginal flora data. This data comprises different species and is recorded at baseline (week 0), and at 3 (group A) or 4 (group B) time points during CVR use.

The presence/absence of each species during CVR use will be analyzed using repeated measures logistic regression models, with random intercepts and random slopes over time for each woman and fixed effects for randomization group (intercept and slope).

For species which are present in the vaginal microbiome of the majority of women and remain present throughout the study, mixed-effects linear regression models will be fitted on the log-transformed bacterial counts. As in the logistic regression models, random intercepts and random slopes over time for each woman and fixed effects for randomization group (intercept and slope) will be included in the linear regression model.

In addition, overall counts of different species may be pooled (e.g., of all *Lactobacillus* species, or all *Lactobacillus* species excluding *L. iners*) and analyzed using mixed-effects linear regression. As an alternative approach, a principal component analysis (PCA) will be performed on the qPCR data and the PCA scores analyzed using mixed effects linear regression. It is expected, based on preliminary analyses of previous dataset, that the first principal component of the flora composition may indicate a gradient from a healthy to a less stable microflora. Changes in the scores for this principal component may consequently indicate deleterious changes in the microbiome. Changes in the second and third principal component will also be explored if they appear to have a reasonable interpretation.

Effects over time will be described as odds-ratio's or changes in log-counts over each 4 week period together with 95% confidence intervals. Effects of the randomization group will be tested at the 5% level (two-sided).

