#### **11.1.1. Study Objectives and Variables of Interest**

The primary and secondary objectives of this clinical trial are to assess the impact on the vaginal microbiome of the use of a vaginal ring intermittently (3 weeks followed by 1 week off) or continuously (primary objective), to assess the general safety of the CVR (secondary objective 1), to assess vaginal biofilm formation and, to detect the presence or absence of a biofilm on the CVRs after intermittent or continuous use (secondary objective 2), and to determine the impact of intermittent or continuous use of the CVR on markers of inflammation and immune activation in the vagina (secondary objective 3).

The objectives will be reached by describing and comparing the variables of interest in women randomized to either intermittent vaginal ring use (group A) over a 12 week study period or continuous ring use (group B) over a 13 week study period.

The variables of interest are:

*Primary:* Changes from baseline (pre-ring use) in vaginal bacterial counts and in the absence/presence of BV-related bacteria as measured with quantitative real time PCR. Specifically, the flora species under study will include (but may not be limited to) the following species

- a. Total *Lactobacillus* count
- b. *Lactobacillus crispatus*
- c. *L. iners*
- d. *L. jensenii*
- e. *L. gasseri*
- f. *L. vaginalis*
- g. *Atopobium vaginae*
- h. *Gardnerella vaginalis*

*Secondary:*

1. Incidence of self-reported vaginal symptoms and clinician-observed signs  
Specifically:
  - a. Incidence of self-reported urogenital symptoms: any ring-use emergent cases of irritation, burning, itching, discharge, bleeding, pain
  - b. Incidence of genital signs on examination: any ring-use emergent cases of vaginal discharge, erythema, edema, ulcer, condyloma, petechia, ecchymosis, peeling
2. Incidence of BV as defined as a Nugent score >6
3. The numbers of women prematurely withdrawing from the study or discontinuing ring use
4. Incidence of adverse experiences during ring use and serious adverse experiences during or within 7 days after ring use
5. The numbers of incident STIs (HIV, HSV-2, Syphilis, Trichomoniasis, Chlamydia, Gonorrhea) and candidiasis
6. Nugent scores and Ison & Hay grading of the vaginal flora
7. Changes in phenotype of BV-related bacteria: specifically
  - i. Presence of dispersed forms of bacteria
  - ii. Presence of adhesive forms of bacteria on epithelial cells

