#### **11.1.3. Sample size and power**

The clinical study sample size calculation is based on the primary objective to assess the pre-post changes in the vaginal microbiome. We require 95% power to detect clinically important changes in bacterial counts. Preliminary analyses of our on-going biomarkers study showed a difference of (-)1 log in overall *Lactobacillus* sp. counts and of (+)3 log in *G. vaginalis* counts between participants with and without BV as assessed by Nugent score, and standard deviations of 1 and 3 for changes in overall *Lactobacillus* sp. counts and *G. vaginalis* counts, respectively. We have defined a change in bacterial count of 50% of the observed differences between women with and without BV as clinically important. Given this, we require 52 women in each study group. To correct for early withdrawals and women lost-to-follow up, we will randomize 120 women (60 in each study group) to ensure we have 104 women with primary endpoint data available.

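### The primary models give one straight time slope and no stated role for baseline, so the change from pre-ring baseline that defines the endpoint and sizes the trial is not estimated as such

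*Protocol*

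**What the plan says.** Section 11.1.1 of the protocol defines the primary variable as "Changes from baseline (pre-ring use) in vaginal bacterial counts", together with the absence or presence of BV-related bacteria. Section 11.1.3 sizes the trial on the same quantity: the calculation is "based on the primary objective to assess the pre-post changes in the vaginal microbiome".

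Section 11.1.2.3 lists the qPCR data as one baseline sample plus 3 (group A) or 4 (group B) samples during ring use. For species presence it states: "The presence/absence of each species during CVR use will be analyzed using repeated measures logistic regression models". The terms are "random intercepts and random slopes over time for each woman and fixed effects for randomization group (intercept and slope"). The log-count model takes the same terms, but no sentence limits it to on-ring samples. Time effects are to be reported as odds ratios or log-count changes per 4-week period. For the comparison of regimens it says only "Effects of the randomization group will be tested at the 5% level (two-sided").

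Section 11.1.2.1 excludes women who lack a sample before or during ring use from analyses that need samples, so a baseline sample is required. No text says whether baseline is an outcome at time zero, a covariate, or the reference for a change score.

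**The concern.** A hormonal ring could shift the flora soon after first insertion, and the shift could then hold. That is a change from baseline, and the sample size is meant to detect it. A single slope describes something else: steady drift per unit of time. If the primary models are fitted as written, the trial could end with slopes and odds ratios per 4 weeks and no direct estimate of the pre-ring to on-ring change, although every sample needed for it was collected.

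**Working it through.** **Inputs.**
- Protocol 11.1.3: clinically important change is half of 1 log for *Lactobacillus* (0.5) and half of 3 log for *G. vaginalis* (1.5); SDs of change 1 and 3; power 95%; 52 per group.
- Protocol 11.1.2.3: two-sided 5% level, stated for the group effect.
- Protocol 8.1.2 and 8.1.8: swabs at ring removal, which is 3, 7 and 11 weeks after enrolment in group A and 3, 6, 9 and 12 weeks in group B.
- Assumption: baseline is placed at time 0.

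**Step 1. What the stated sample size is for.** For a paired change within one group, n = ((1.960 + 1.645) × SD / change)² = (3.605 × 1 / 0.5)² = 51.98, so 52. The *G. vaginalis* values give the same result, since 1.5/3 = 0.5/1. A comparison of change between two groups would need 2 × 51.98 = 103.96, so 104 per group. The stated 52 therefore belongs to the within-group pre-post change.

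**Step 2. On-ring samples only.** Let the true mean be 0 at baseline and 0.5 at every on-ring visit. The on-ring values are 0.5, 0.5, 0.5 in A and 0.5, 0.5, 0.5, 0.5 in B. The slope is 0 in both arms. On the presence/absence scale, a persistent shift in log odds likewise gives an odds ratio of 1 per 4 weeks.

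**Step 3. Baseline added to the same line.** Slope = Σ(t − t̄)y / Σ(t − t̄)².
- Group A, t = 0, 3, 7, 11, t̄ = 5.25: numerator 0.5 × (−2.25 + 1.75 + 5.75) = 2.625; denominator 27.5625 + 5.0625 + 3.0625 + 33.0625 = 68.75; slope 0.0382 per week, or 0.153 per 4 weeks.
- Group B, t = 0, 3, 6, 9, 12, t̄ = 6: numerator 0.5 × (−3 + 0 + 3 + 6) = 3; denominator 36 + 9 + 0 + 9 + 36 = 90; slope 0.0333 per week, or 0.133 per 4 weeks.

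With the protocol's week labels (0, 4, 8, 12 and 0, 4, 7, 10, 13) the results are 0.150 and 0.132. With complete data and the same visit times for all women in an arm, random intercepts and slopes leave these mean slopes unchanged.

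**Step 4. The gap between arms.** The true change is identical, yet the slopes differ by 0.153 − 0.133 = 0.02 log per 4 weeks. By generalized least squares with 52 per group and SD of change 1, a nominal 5% test of the group slope then rejects 6.1% of the time (5.9% with an assumed random-slope SD of 0.04 per week). This distortion is real but small.

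**Step 5. A model with the missing term.** With a common baseline, a step at first ring use, an on-ring slope and a group slope after the first ring, the same calculation returns a step of 0.500, and the group-slope test rejects 5.0% of the time.

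**The case against.** The protocol promises a statistical analysis plan before database lock (section 11.1), and time coding and contrasts are often left to that plan. This stands for what the protocol leaves open. It does not cover what the protocol fixes: linear time, a group intercept and slope, reporting per 4 weeks and, for presence/absence, data during ring use. A plan that follows this text inherits the mismatch.

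A linear mixed model is a fair choice if change is expected to build up gradually over successive rings. One could also multiply the slope up: 0.0382 × 11 = 0.42 in A and 0.0333 × 12 = 0.40 in B, not far from 0.5. But nothing plans that readout. The fitted line also puts baseline at 0.375 − 0.0382 × 5.25 = 0.17 in A and 0.4 − 0.0333 × 6 = 0.20 in B, where the truth is 0.

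Three stronger readings are tempting, and the documents do not support them.
- **A reader might infer that the log-count model also uses only on-ring data.** The restriction is written for presence/absence alone. Listing baseline among the primary data and requiring a pre-ring sample suggest that baseline was meant to be used for counts. The fault there is an unstated role plus a single slope.
- **A reader might infer that the week-4 visit wastes power**, because both arms have worn one ring for 3 weeks by then. The visit anchors the slope. In an on-ring model with a group difference growing linearly from 0 at week 4 to 0.5 log at the last group B visit (52 per group, no random-slope variance), dropping it cuts slope-test power from 69% to 27%.
- **A reader might infer a joint two-degree-of-freedom test of group intercept and slope with 68 to 93% power.** The protocol names no such test. Those figures need on-ring data only, a full 0.5 log regimen difference straight after week 4, no random-slope variance and correlations of 0.3 to 0.7. With baseline included and no common first-ring shift, the same joint test has 87 to 96%.

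**Conclusion.** The concern holds in limited form. The endpoint and the sample size concern change from baseline. The presence/absence model as worded leaves the baseline sample out, and both primary models carry one straight slope per 4 weeks with no stated place for baseline. For a persistent 0.5 log shift at first ring use, the reported time effect is 0 without baseline, or about 0.15 (A) and 0.13 (B) log per 4 weeks with it.

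The size depends on the shape of the change. If change is truly linear from baseline, a model that includes baseline is adequate. If it is abrupt, neither version reports it. The protocol gives no reason to rule out the abrupt case.

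No general claim about lost power for the regimen comparison follows. That depends on effect shape, within-woman correlation and slope variance, none of which the protocol gives.

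**What to change.** Amend section 11.1.2.3, and carry the change into the analysis plan, as follows.

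1. Include the baseline sample as an outcome in both the presence/absence and the log-count models.
2. Model the pre-ring to on-ring change explicitly, either with visit as a category or with an on-ring step plus an on-ring slope.
3. Pre-specify two primary contrasts: on-ring minus baseline within each regimen, and the difference between regimens in that change. Name the visits that are averaged.
4. Keep the effect per 4 weeks as a description of on-ring drift.

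A common group mean at baseline may be imposed, because randomization follows that sample. A common mean at week 4 is optional: treatment is the same up to that swab, but allocation is open and visit windows differ by arm. The gain in precision is not assured. With linear divergence to 0.5 log, no common first-ring shift and a random-slope SD of 0.04 per week, a model with both means held equal and one average group effect after week 4 has 60 to 67% power. A baseline-inclusive group-slope test has 72%.

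The cost is wording only; no visit or sample is added. Section 11.1.3 should also say that 52 per group gives 95% power for the within-regimen contrast. A 0.5 log regimen difference in a single change score has about 72%: 0.5/√(2/52) = 2.55, and 2.55 − 1.96 = 0.59 on the normal scale.

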#### 11.1.2.4. Secondary analyses

The incidence of signs and symptoms, study/ring use withdrawals, adverse experiences, and STIs will be compared among randomization groups over the full study period using Fisher's exact test. Changes in Nugent scores and Ison & Hay grading of the vaginal flora will be graphically depicted and analyzed using repeated measures (logistic) regression models.

Analyses of endpoints related to secondary objectives 2 and 3 will be research and data driven. Presence/absence of dispersed/adherent form of BV-related bacteria and of biofilms will be analyzed using repeated measures logistic regression models.

Analyses of CVLs will focus on changes from baseline in cytokine concentrations. Care will be taken to mitigate the influence of truncation of the concentration data due to samples below or above the quantification limit of the assays used. Data reduction techniques as PCA may be used to summarize the multidimensional data in a limited number of variables. All samples that are showing elevated cytokine levels, as well as an equal number of controls not showing elevated cytokine levels, will be tested further for the presence of other proteins involved in inflammatory pathways. Control samples will be selected matched on major prognostic factors.

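### Fisher tests on full-period incidence give group B four examination visits and group A three, which shifts visit-detected safety findings against continuous use

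*Protocol*

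**What the plan says.** Section 11.1.2.4 fixes both the test and the window. The incidence of signs and symptoms, withdrawals, adverse experiences and STIs "will be compared among randomization groups over the full study period using" Fisher's exact test. It mentions no exposure offset, common window or visit-level model. The next sentence gives Nugent and Ison & Hay data repeated-measures models.

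Section 11.1.1 defines the endpoints:

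- Symptoms: "Incidence of self-reported urogenital symptoms: any ring-use emergent cases of irritation, burning, itching, discharge, bleeding, pain".
- Signs: "Incidence of genital signs on examination: any ring-use emergent cases of vaginal discharge, erythema, edema, ulcer, condyloma, petechia, ecchymosis, peeling".
- Adverse events: "Incidence of adverse experiences during ring use and serious adverse experiences during or within 7 days after ring use".

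The number of assessments differs by arm. Section 8.1.3 places the pelvic examination, vaginal swabs (including wet mount) and questionnaire at ring-removal visits. The schedule in section 8.1.8 has removals at weeks 4, 8 and 12 in group A (V2, V4, V6) and weeks 4, 7, 10 and 13 in group B (V2 to V5). Section 11.1.2.3 confirms the count for the qPCR samples: "at 3 (group A) or 4 (group B) time points during CVR use". Section 11.1.1 also gives group A a 12-week period, against "continuous ring use (group B) over a 13 week study period".

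**The concern.** A Fisher test on any emergent case compares, per woman, ever against never. That proportion grows with the number of occasions on which a finding can be recorded. With three occasions in one arm and four in the other, the two proportions differ even when the regimens carry the same risk at each visit. The direction is fixed: group B looks worse.

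General safety is secondary objective 1. The rationale in section 4.2 is that a multi-purpose ring would have to be used continuously. A built-in excess of genital signs, symptoms, trichomoniasis or candidiasis in the continuous arm would distort the comparison that motivates the trial.

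**Working it through.** **Inputs.** Visits with examination, wet mount and questionnaire: 3 in A, 4 in B (sections 8.1.3 and 8.1.8). Women: 60 per group (section 5.2). Two-sided 5% level: stated only for the primary analysis (section 11.1.2.3) and assumed here. The protocol gives no event rate, power or sample size for these tests, so there is no planned figure to reproduce. The risk per visit q is an assumption, taken over 5–20%.

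**Step 1: equal risk, independent visits.** The proportion ever positive is 1 − (1 − q)^3 in A and 1 − (1 − q)^4 in B. At q = 10% this is 1 − 0.729 = 27.1% and 1 − 0.6561 = 34.4%, a difference of 7.3 points.

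**Step 2: equal risk, correlated visits.** Signs in the same woman are likely to recur, so independence is the extreme case. Take a beta-binomial model with within-woman correlation ρ, s = (1 − ρ)/ρ and b = (1 − q)s. The chance of no positive visit in k is the product over j = 0, …, k − 1 of (b + j)/(s + j). At q = 10% and ρ = 0.2, s = 4 and b = 3.6. Three visits give 0.900 × 0.920 × 0.933 = 0.773, so 22.7% ever positive. A fourth factor of 6.6/7 gives 0.729, so 27.1%.

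**Step 3: exact Fisher rejection, 60 per group**, by enumerating all pairs of counts:

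| Correlation | q per visit | A (3 visits) | B (4 visits) | Risk ratio | Rejects |
|---|---|---|---|---|---|
| 0 | 5% | 14.3% | 18.5% | 1.30 | 5.9% |
| 0 | 10% | 27.1% | 34.4% | 1.27 | 9.8% |
| 0 | 20% | 48.8% | 59.0% | 1.21 | 16.3% |
| 0.2 | 5% | 11.8% | 14.4% | 1.21 | 3.8% |
| 0.2 | 10% | 22.7% | 27.1% | 1.19 | 5.6% |
| 0.2 | 20% | 41.8% | 48.4% | 1.16 | 8.6% |
| 0.5 | 5% | 8.9% | 10.1% | 1.13 | 2.4% |
| 0.5 | 10% | 17.3% | 19.4% | 1.12 | 3.4% |
| 0.5 | 20% | 32.8% | 36.2% | 1.10 | 4.3% |

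With three visits in both arms and independent visits, the test rejects in 2.6%, 3.0% and 3.5% at q = 5%, 10% and 20%. Under independence nearly all rejections go against B. At ρ = 0.3 the rejection rates for 10% and 20% are 4.6% and 6.5%.

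**Step 4: adverse events.** Read literally, "Incidence of adverse experiences during ring use" counts 3 × 3 = 9 weeks in A and 4 × 3 = 12 weeks in B. With an equal weekly hazard, A = 1 − (1 − B)^(9/12), so 30% in B corresponds to 23.5% in A, and 40% to 31.8%. If the count instead runs from first insertion to final removal, ring-free weeks included, the windows are 11 weeks in A (week 1 to week 12) and 12 weeks in B (week 1 to week 13). Then A = 1 − (1 − B)^(11/12), which gives 27.9% against 30% and 37.4% against 40%. The literal reading produces most of the gap.

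**The case against.** **The error rate.** A reader might infer that these tests carry a false-positive rate of 10–16%. The documents do not support that. It needs 10–20% positive per visit and independent visits. The only frequency given is in section 14.5: headaches and vaginal infections in 5–6% of women, with no period stated. Taking 5.6% over three visits means about 1.9% per visit, hence 5.6% against 7.4%, and Fisher rejects in 2.3% even under independence. Composite signs or symptoms may be commoner, but no rate is given. This part of the objection stands, and it limits the type I error claim.

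**Adverse events.** A reader might also take 9 against 12 weeks as settled. Section 11.1.2.4 speaks of the full study period, section 10.1.3 collects adverse events until the final ring removal, and section 8.1.3 asks about them at group A's insertion visits, straight after the ring-free weeks. Serious events count for 7 days after ring use, which covers a ring-free week. Adverse events are also elicited at five contacts in A (V2 to V6) and four in B (V2 to V5), which partly works the other way. So the size of any adverse-event bias is open.

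**STIs.** HIV is tested at the last ring-removal visit in each arm, and no follow-up test is listed for chlamydia, gonorrhoea, syphilis or HSV-2. The three-against-four imbalance touches only wet-mount trichomoniasis and candidiasis.

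**The estimand.** More ring time is part of continuous use, so counting harms over the assigned course is a legitimate comparison of regimens. That is fair for exposure. It does not justify an extra examination, which is detection opportunity.

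**The statistical analysis plan.** Section 11.1 promises one for this objective, and it may refine the method. But the protocol has already fixed test and window, so the text needs correcting.

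**Conclusion.** The point holds for findings recorded at ring-removal visits: genital signs, questionnaire-reported symptoms, and trichomoniasis and candidiasis on wet mount. At equal per-visit risk, the planned cumulative proportions are biased against continuous use. The risk ratio is about 1.2–1.3 under independence and about 1.1–1.2 with within-woman correlation of 0.2–0.5, for an assumed 5–20% per visit. The direction does not depend on these assumptions, unless a woman's status never changes between visits.

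Inflation of the type I error is conditional: rejection is 6–16% under independence and about 2–9% with that correlation, so it may not exceed 5% at all. For adverse events, the protocol should first settle which window applies. The rest of the STI endpoint is not affected by the visit imbalance. This should be corrected, but it does not threaten the primary analysis.

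**What to change.** 1. Analyse signs, symptoms and wet-mount infections with a visit-level repeated-measures logistic model (GEE or mixed), with randomization group and time or ring number as terms, as section 11.1.2.4 already does for Nugent and Ison & Hay data. State whether a case means present at the visit or new since the last one. After the first removal, group A's removal visits are 4 weeks apart and group B's 3, so a new-onset definition also has to account for interval length.
2. Keep the cumulative proportions as description, with the number of visits per arm beside them.
3. Count adverse events from first insertion to final ring removal, ring-free weeks included, and compare rates per woman-week (Poisson or negative binomial with a log follow-up offset). Bring the wording of sections 11.1.1 and 11.1.2.4 into line.
4. Use a comparison of the first three removals only as a sensitivity analysis. It sets about 11 weeks from insertion in A against 9 in B and drops B's longest exposure, so it favours B for events that accrue with calendar time: 20% in A would correspond to 1 − 0.8^(9/11) = 16.7% in B.

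The cost is analysis wording and slightly more modelling; no visit, sample or participant changes. Rare events may not converge, so name an exact or descriptive fallback. The tested quantity becomes a per-visit or per-week effect rather than a cumulative one, and the report should say so.

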#### **8.1.2. Enrolment visit (at the start of week 1)**

Women will be invited for the enrolment visit which will take place on the first day of their menstrual cycle. (ie. the first day of menstrual bleeding). A visit window of + 1 day will be allowed when the menstrual cycle starts on a Sunday or bank holiday. The visit can be rescheduled maximum once if the participant is not on her first day of menstrual bleeding (+ 1 day).

All test results from the baseline visit will be reviewed, and eligibility will be confirmed. Eligible women will be randomized either to an intermittent regimen (group A) or an extended (continuous) regimen (group B) of ring use.

There will be no re-screenings.

The following procedures will also be carried out:

- The general physical examination will be performed as at baseline.
- All women will be offered risk reduction counselling and condoms free of charge.
- A urine sample will be obtained for pregnancy testing.
- Study staff will teach women how to use the ring and study participants will be asked to insert the ring while still at the study clinic.

- A questionnaire on acceptability of the ring after the ring has been inserted.
- Participants will receive a diary card and will be explained how to complete a diary card regarding ring use and sexual behaviour as well as how to complete a self-rating adherence scale.
- Provide a follow-up visit date: 3 weeks after the enrolment date.

### 8.1.3. Follow up visits: Visits 2 to Visits 6

The follow up visits are planned to coincide with times of removal and insertion of the ring. Women in group A will visit the clinic at days of removal and insertion. These visits will coincide in group B as the old ring will be replaced by a new one at the same visit.

Participants in group B will be allowed to complete each follow-up visit up to three days prior/after their scheduled visit. The visit window for participants in group A (intermittent use) will depend of the kind of visit. Ring removal visits can be delayed for a maximum of 2 days, ring insertion visits can be performed a maximum of 2 days in advance. Every effort should be made to ensure participants adhere to this visit schedule.

The following procedures are performed at each ring removal visit (both study arms):

- Information on adverse events, social harms and concomitant medication will be collected.

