- The pelvic and general physical examinations will be performed as at baseline. A total of 3 vaginal swabs are collected for:
  - One cotton swab for Wet Mount [*Trichomonas vaginalis* (TV); *Candida albicans*] and smears for BV diagnosis;
  - Two regular flocked swabs (Copan, Italy) for the characterisation of the vaginal microbiome.
- At visit 6 for Group A and visit 5 for Group B, after the final ring has been removed and all other vaginal specimens have been collected, a CVL sample will be collected.
- A urine sample is obtained, tested for pregnancy and an aliquot of fixated urine will be stored for FISH analysis.
- A completed diary card will be collected at each visit and a new diary card will be provided. Any problems with ring use will be addressed.
- The removed ring will be processed according to the instructions provided by the ITM and stored for biofilm analysis.
- Risk reduction counselling will be provided as well as condoms (free of charge).
- During the last ring removal visit (V6 for group A and V5 for group B) the following additional procedures will be offered:
  - a Visual Inspection with Acetic acid (VIA) to identify women at risk for cervical cancer;
  - An HIV test according to the national HIV algorithm. A maximum of 5 ml of blood will be collected by venepuncture in a serum tube. Pre- and post-test HIV counselling will be provided.

Additional questionnaires during ring removal visits:

1. The IAQ will be performed at every visit and will assess adherence and acceptability of the ring use but will be more comprehensive at visits 4 and 6 for group A and at visits 3 and 5 for group B. It will also assess factors that might influence the vaginal microbiome and vaginal inflammation.
2. Between weeks 7 and 9, 16-24 women will be enrolled in one of two FGD in each randomization group, for a total of four FGD.

3. At the last ring removal visit, and if funding permits, all study participants will be invited to provide their feedback on experiences with the new contraceptive method, on acceptability and adherence using ACASI.

The following procedures are performed at the ring insertion visits for group A:

- Information on adverse events, social harms and concomitant medication will be collected.
- Risk reduction counselling will be provided as well as condoms (free of charge).

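### The full-period Fisher test of genital signs, removal-visit symptoms and trichomoniasis ignores that group B is examined four times and group A three, which moderately biases transient findings against continuous use

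*Protocol*

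**What the plan says.** Section 11.1.2.4 states: "The incidence of signs and symptoms, study/ring use withdrawals, adverse experiences, and STIs will be compared". The same sentence fixes the method: these endpoints are to be "compared among randomization groups over the full study period using Fisher's exact test". It gives no denominator of visits or time. Section 11.1.1 defines the sign endpoint as any case: "Incidence of genital signs on examination: any ring-use emergent cases of vaginal discharge", followed by a list of other signs. Symptoms are defined in the same way. A Fisher test on such an endpoint classifies each woman once, as ever or never affected.

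Section 8.1.3 ties the examinations to ring removal. Its list opens "The following procedures are performed at each ring removal visit (both study arms" and includes "The pelvic and general physical examinations will be performed as at baseline", with the swab for wet mount (trichomonas, candida). The schedule in section 8.1.8 puts these visits at weeks 4, 8 and 12 in group A and weeks 4, 7, 10 and 13 in group B. Section 11.1.2.3 gives the same counts for the qPCR samples: "at 3 (group A) or 4 (group B) time points during CVR use".

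Group A also has two insertion-only visits (V3, V5). Section 8.1.3 introduces them with "The following procedures are performed at the ring insertion visits for group A"; adverse events are asked about there, but no pelvic examination is listed.

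For qPCR, Nugent scores and Ison & Hay grading, the protocol plans repeated-measures models.

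**The concern.** If a finding comes and goes, the chance that it is seen at least once rises with the number of times someone looks. Four looks against three is a feature of the schedule, not an effect of the regimen, and the planned test cannot tell the two apart. The bias runs against continuous use, the regimen that the rationale (section 4.2) says a future multi-purpose ring would require. It could suggest a harm that is not there or conceal a real advantage. The protocol names this test itself, so the choice has not been left to the statistical analysis plan, and it contrasts with the repeated-measures approach used for the other examination-based outcomes.

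**Working it through.** **Inputs from the protocol.** Scheduled on-ring examinations: k = 3 (A) and k = 4 (B), sections 8.1.3 and 8.1.8. Randomized women: 60 per group, section 7.3. Time from first insertion to last removal:
- A: 3 + 1 + 3 + 1 + 3 = 11 weeks = 77 days
- B: 4 × 3 = 12 weeks = 84 days

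These agree with week labels 12 and 13 when enrolment is at the start of week 1. The protocol gives no expected event rate or power for the Fisher comparisons, so there is no stated figure to reproduce beyond the visit counts.

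**Assumptions.** Per-examination risk p = 5%, 10% or 20%, equal in both groups. Within-woman correlation 0 or 0.3. Two-sided 5% level (stated for the primary analysis, assumed here). Rejection probabilities come from full enumeration of Fisher's exact test at 60 v 60.

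**Case 1: transient finding, independent visits.** P(ever) = 1 − (1 − p)^k. At p = 10%: A = 1 − 0.9³ = 27.1%; B = 1 − 0.9⁴ = 34.4%.

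**Case 2: transient finding, correlation 0.3 (beta-binomial).** At p = 10% the beta parameters are 0.2333 and 2.1, which sum to 2.3333.
- P(none in 3) = (2.1/2.3333)(3.1/3.3333)(4.1/4.3333) = 0.792, so A = 20.8%.
- Multiplying by 5.1/5.3333 gives 0.757, so B = 24.3%.

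**Case 3: persistent finding, equal weekly risk.** Each event is still detectable at the next visit, so only time matters. Keeping A at its case 1 value, B = 1 − (1 − A)^(84/77). At A = 27.1%: B = 1 − 0.729^1.0909 = 29.2%.

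| p per examination | Case 1: A v B (rejects) | Case 2: A v B (rejects) | Case 3: A v B (rejects) |
|---|---|---|---|
| 5% | 14.3% v 18.5% (5.9%) | 10.8% v 12.7% (3.2%) | 14.3% v 15.5% (2.9%) |
| 10% | 27.1% v 34.4% (9.8%) | 20.8% v 24.3% (4.6%) | 27.1% v 29.2% (3.6%) |
| 20% | 48.8% v 59.0% (16.3%) | 38.6% v 44.0% (6.5%) | 48.8% v 51.8% (4.5%) |

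With three examinations in both groups and independent visits, the same test rejects in 2.6%, 3.0% and 3.5% of trials. In case 1, more than 96% of rejections have B worse.

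**Masking.** In case 1, the ever-affected proportions are equal when B's risk per examination is 1 − (1 − p)^(3/4). At p = 10% this is 7.6%, so a 24% lower risk under continuous use would show as no difference.

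**Which endpoints are exposed.**
- Genital signs and trichomoniasis by wet mount: yes.
- Symptoms: to the extent that they are asked about at removal visits (3 v 4).
- Candidiasis: only if it is analysed with the STIs. Section 11.1.1 pairs the two, but the Fisher list in 11.1.2.4 names only STIs.
- HIV: one test at the last removal visit in each group, so no.
- Chlamydia, gonorrhoea, HSV-2 and syphilis: no scheduled follow-up test is listed.
- Withdrawals: they do not depend on examinations.
- BV: Nugent scores already have a repeated-measures model.

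**The case against.** The best counter-argument is that equal risk per examination is not the only way to state that the regimens do not differ. After week 4, A's intervals are four weeks and B's three. For a condition that lasts until the next visit, the neutral assumption is equal risk per week. The gap is then 1 to 3 points and Fisher's test stays below its nominal level (case 3). Unscheduled visits and syndromic diagnosis (sections 8.1.5 and 8.4) also catch some events in both groups. All of this stands. It limits the size of the problem but does not remove it for transient signs. Fisher's test is also a reasonable choice for very sparse events.

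A reader might infer that adverse events are distorted too, because A is asked about them five times and B four. Treating each interview as a separate 10% chance gives 41.0% v 34.4% (1 − 0.9⁵ v 1 − 0.9⁴). The documents do not support that figure. An interview covers the time since the last contact, and section 10.1.3 asks women to report problems themselves. Abnormal laboratory findings also count as adverse events (section 10.1.1), and wet mounts are more frequent in B, so no net direction is established.

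**Conclusion.** The concern holds for transient findings made at scheduled examinations, and for symptoms asked about at removal visits. With no regimen effect, B's excess at 10% per examination is 7.3 points if visits are independent (34.4 − 27.1) and 3.5 points at correlation 0.3. Fisher's rejection rate is about 10% and 4.6% respectively. For persistent findings the excess is only about 1 to 3 points, with rejection below 5%. The per-examination risks, the correlation and the degree of persistence are assumptions, because the protocol gives none of them.

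The distortion is therefore moderate and depends on persistence. A reader might conclude that the regimen safety comparison as a whole cannot be interpreted. That goes too far: withdrawals, HIV and the Nugent analysis are not affected, and the adverse-event comparison has no demonstrated direction of bias. Part of any difference may also be real exposure, since the ring is in place for 9 weeks in A (3 × 3) and 12 in B (4 × 3). The planned test cannot separate that from the extra examination.

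**What to change.** Change section 11.1.2.4, and carry the change into the analysis plan that section 11.1 requires before database lock:

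- For genital signs, trichomoniasis, candidiasis and symptoms asked about at removal visits, compare the groups per examination with a repeated-measures logistic model, with woman as cluster and week of examination as covariate. This is the type of model already planned for Nugent scores. Where events are too sparse for it, compare over matched examinations.
- Compare adverse events as onset-dated rates per woman-week, using every reported event. Do not drop those first reported at V3 or V5: that would remove events from group A only and create a bias against B.
- Keep the ever/never counts with Fisher's test as description.
- Leave BV (Nugent), HIV and withdrawals as planned.

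The cost is a change of wording and slightly more analysis work, with no new visits, data or participants. The drawback is that the per-examination model estimates prevalence at examinations, so a persistent finding counts more than once. It does not estimate first occurrence, which is why the descriptive counts should stay beside it.
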